#### **Late Follow-Up Visit**

Late follow-up (28 to 35 days after last dose of study drug) will be conducted by telephone unless an examination is needed to evaluate relapse (need for further antibiotic treatment) or abnormalities that were present at TOC visit.

## **9.2. Pharmacokinetic Evaluations\***

All subjects will participate in either sparse or rich PK sampling.

### **9.2.1. Sample Collection and Handling\***

Refer to the PK laboratory manual, which will be provided as a separate document (refer to Section 14, Study-Specific Materials) for information regarding handling of biological samples. The exact dates and times of blood sampling must be recorded either in the CRF or the laboratory requisition form as appropriate.

#### **At selected sites for rich PK sampling:**

Seven blood samples and 1 urine sample (over 8 hours) for each subject will be obtained for PK analysis at selected sites with appropriate facilities and equipment. Approximately 120 subjects (approximately 60 subjects on ceftobiprole treatment and approximately 60 subjects on ceftriaxone with or without linezolid) will participate in PK sample collections. The selected

---

\* This section of the protocol has been revised. Please refer to the section of this document entitled PROTOCOL AMENDMENTS (Amendment INT-3, 22 December 2006) for a detailed description of the specific changes.

\* This section of the protocol has been revised. Please refer to the section of this document entitled PROTOCOL AMENDMENTS (Amendment INT-3, 22 December 2006) for a detailed description of the specific changes.

sites may also include some elderly subjects (>65 years) for the PK sampling if they are available.

On Day 4 $\pm$ 1, one 3 mL blood sample will be obtained immediately before the start of the 120-minute morning infusion (predose); subsequent 3-mL blood samples will be obtained at 15 minutes, 1, 2 (immediately before the end of infusion), 4, 6, and 8 hours after the start of the morning infusion. On this day, subjects will be asked to void and discard urine immediately before the start of the infusion. Subsequently, urine will be collected during the period of 0 to 8 hours after the start of the 120-minute morning infusion. Subjects will be encouraged to drink water ad libitum.

Subjects may refuse to participate in rich PK blood sampling and still be enrolled in the study. In this circumstance, sparse PK samples should be collected for these subjects.

#### **At sites for sparse PK sampling:**

Three sparse PK blood samples will be collected for each subject who does not participate in the rich PK sampling. On study Day 1, 2 PK blood samples (3 mL each) will be taken; one at approximately 2 hours (or immediately before the end of the first 120-minute infusion) and the other 6 hours after the start of this infusion (the first dose of the entire treatment). On Day 4 $\pm$ 1, another PK blood sample (3 mL) will be taken at any time during the dosing interval, but starting at least 30 minutes after the onset of this 120-minute morning infusion. No PK urine sample will be collected for subjects with sparse sampling.

#### **9.2.2. Analytical Procedures**

Plasma samples will be analyzed for ceftobiprole by a validated specific liquid chromatography coupled to tandem mass spectrometer (LC-MS/MS) method. Urinary concentrations of ceftobiprole will be analyzed by LC-MS/MS. The sponsor or its designee will perform all analyses.

### 9.2.3. Pharmacokinetic Parameters\*

In order to develop a structural PK model of ceftobiprole and to evaluate the dependence of PK of the active ceftobiprole on population covariates, all PK data from subjects in this study with both rich and sparse sampling will be combined with data from other clinical studies of ceftobiprole for a pooled population PK analysis. This pooled analysis will be reported separately.

Pharmacokinetic parameters will be derived by noncompartmental analysis using WinNonlin™ (Version 4.0.1 or an upgraded version if available, Pharsight Corporation, California). Pharmacokinetic parameters will include  $AUC_{\tau}$ ,  $C_{\max}$ , CL, and Ae of ceftobiprole. In addition, time above MIC of ceftobiprole will be determined (assuming MIC of 4 µg/mL).

- $C_{\max}$  maximum drug concentration observed in plasma
- $AUC_{\tau}$  area under the plasma concentration versus time curve from time during the dosing interval ( $\tau = 8$  hours)
- CL Total systemic clearance, estimated by dose/ $AUC_{\tau}$
- Ae Amount excreted into the urine, calculated by the product of urinary volume times the urinary concentration over the collection interval

Plasma concentrations at each time point of measurement will be evaluated by descriptive statistics, including arithmetic mean, standard deviation, minimum, maximum, and median.

All PK parameters will be presented in listings and using descriptive summary statistics.

For subjects with sparse PK sampling, plasma concentrations will be listed with the corresponding sampling time for all subjects.

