### **Rationale for PK Assessments**

In order to develop a PK structure model and evaluate the dependence of the PK of the active ceftobiprole on subject population covariates, collection of PK samples with rich sampling in a limited number of subjects and with sparse sampling in additional subjects are needed.

The combination of rich PK sampling and sparse PK sampling will be utilized to explore the effects of age, sex, weight, and renal function on plasma ceftobiprole concentrations.

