## JNJ-30982081: Clinical Protocol 30982081-CAP-3001 - Amendment INT-3

- History of or suspected condition that may jeopardize adherence to protocol requirements (e.g., severe cardiac disease such that even minimal physical activity causes discomfort, New York Heart Association [NYHA] Class 4)
- History of or suspected hypersensitivity to any related anti-infective (including beta-lactam antibiotics such as penicillins and cephalosporins, oxazolidinones). Subjects in whom cephalosporins would be used as part of normal clinical practice are not excluded.
- History of or suspected condition or concurrent treatment that would be contraindicated by the prescribing information for ceftriaxone or linezolid
- History of or suspected severe renal impairment, (i.e.,  $Cl_{Cr} \leq 30$  mL/min or oliguria  $<20$  mL/h unresponsive to fluid challenge) or any form of dialysis
- History of or suspected hepatic dysfunction (total bilirubin, or alanine aminotransferase [ALT], or aspartate aminotransferase [AST]  $\geq 3$  times the upper limit of the normal range [ULN]).
- History of suspected extra-pulmonary infection, including concomitant meningitis, endocarditis, septic arthritis, or osteomyelitis
- Known to be human immunodeficiency virus (HIV) positive with CD4 counts of  $\leq 0.2 \times 10^9/L$  ( $\leq 200$  cells/mm^3). (Subjects with HIV and  $>0.2 \times 10^9/L$  [ $>200$  cells/mm^3] may be included)
- Presence of neutropenia, (absolute neutrophil count [ANC]  $\leq 0.5 \times 10^9/L$  [ $<500$  Neutrophils [polymorphonuclear leukocytes] [PMNs/mm^3]) severe anemia (hemoglobin  $<6.5$  g/dL), or severe thrombocytopenia ( $<49.9 \times 10^9/cm$ ). *Note: Subjects receiving immunosuppressive therapy who are expected to reach a nadir of  $<500$  PMNs/mm^3 during administration of study drug should not be enrolled*
- Previous enrollment in this study or any other ceftobiprole protocol
- Have received an experimental drug or used an experimental medical device within 30 days before the planned start of treatment
- Is pregnant or breast-feeding
- Employees of the investigator or study center, with direct involvement in the proposed study or other studies under the direction of that investigator or study center, as well as family members of the employees or the investigator

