#### **6.1.2. Intravenous and Oral Switch Study Drug Regimen**

Study drug (i.v. plus oral) will be administered for 5 to 10 days. The total duration of study drug therapy (i.v. plus oral) for all subjects will be a minimum of 5 days and a target of 7 days. If, in the investigator's opinion, a subject requires additional days of study therapy, the duration of the therapy may be extended (up to a maximum of 10 days). Therapy can be extended to a maximum of 14 days after approval by the sponsor's Medical Monitor, for subjects with a history of persistent bacteremia or X-ray evidence of necrotizing pneumonia.

At the investigator's discretion, therapy may be stopped when the infection is considered clinically cured (based on normalization of the clinical signs and symptoms of infection and improvement in the chest X-ray, and after a minimum of 5 total treatment days).

Ceftobiprole and ceftriaxone will be administered as follows:

- Ceftobiprole will be administered at a dose of 500 mg in 250 mL of 5% dextrose in water (D5W) every 8 hours at a constant-rate i.v. infusion over a period of 120 minutes (must not be administered through an i.v. line containing sodium chloride [e.g., saline, Ringer's Lactate solution]). Further details of the preparation and administration of ceftobiprole are presented in Attachment 2, Preparation and Administration of Intravenous Infusion Solutions of Ceftobiprole Medocaril (500 mg dose).
- Ceftriaxone will be administered at a dose of 2 g in 50 mL of D5W every 24 hours by i.v. infusion over a period of 30 minutes.

Placebo will be used to maintain the blind for both cephalosporins:

- For subjects randomized to ceftobiprole, a 30-minute i.v. infusion of placebo of 50 mL of D5W will be given every 24 hours concomitantly with ceftobiprole and will begin with the first dose of ceftobiprole.
- For subjects randomized to ceftriaxone, a 120-minute i.v. infusion of placebo of 250 mL of D5W will be given every 8 hours concomitantly with ceftriaxone, and will begin with the first dose of ceftriaxone.

Note: The 30-minute infusion should be administered first (placebo or ceftriaxone), followed by the 120-minute infusion (ceftobiprole or placebo), to ensure that active treatment is delivered to the subject as soon as possible.

Optional oral switch regimen:

- Cefuroxime axetil 500 mg every 12 hours orally.

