#### **6.1.4. Dose Adjustment for Renal Impairment**

Dose adjustment for renal impairment will be made according to  $Cl_{Cr}$  at enrollment and will be adjusted if there are any changes during the study. Additional assessments of serum creatinine or renal function may be performed at the local laboratory at any time during the study, as clinically indicated. NOTE: Although subjects with  $Cl_{Cr}$  of  $\leq 30$  mL/min are initially excluded, if a subject's  $Cl_{Cr}$  decreases to  $\leq 30$  mL/min after enrollment they may remain in the study and the dosage of study drug(s) should be changed accordingly. Placebo infusions should be added as needed to maintain the blind.

- Cefetobiprole: in subjects with moderate renal impairment ( $Cl_{Cr} > 30$  to  $\leq 50$  mL/min) cefetobiprole will be infused at a dose of 500 mg every 12 hours over 120 minutes. In subjects with severe renal impairment ( $Cl_{Cr} > 10$  to  $\leq 30$  mL/min) 250 mg of cefetobiprole will be infused every 12 hours over 120 minutes. Subjects whose  $Cl_{Cr}$  level falls to  $\leq 10$  mL/min are to be discontinued from the study.
- Ceftriaxone: No adjustment of ceftriaxone is recommended in subjects with renal impairment provided the daily dose is 2 g/day or less. To maintain the blind, subjects with  $Cl_{Cr} \leq 50$  mL/min, will receive placebo 2-hour infusions every 12 hours instead of every 8 hours.
- Linezolid: No adjustment is required.
- Cefuroxime axetil: Do not use in subjects with  $Cl_{Cr} < 30$  mL/min.

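### Noncompartmental AUC and clearance use an 8-hour interval for every subject, although renally impaired subjects are dosed every 12 hours; their clearance would be overstated by about 15 to 21% or more

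*Protocol*

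**What the plan says.** Section 9.2.3 (Pharmacokinetic Parameters) lists the noncompartmental parameters. AUCtau is the "area under the plasma concentration versus time curve from time during the dosing interval", followed in brackets by tau = 8 hours. CL is "Total systemic clearance, estimated by dose" over that AUCtau. No other tau is given for any subject.

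Eight hours matches the standard regimen in section 6.1.2, 500 mg "every 8 hours at a constant-rate i.v. infusion over a period of 120 minutes". Section 6.1.4 departs from it. With creatinine clearance above 30 to 50 mL/min, ceftobiprole "will be infused at a dose of 500 mg every 12 hours over 120 minutes". With creatinine clearance above 10 to 30 mL/min, 250 mg "will be infused every 12 hours over 120 minutes".

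Both groups can occur. Section 4.3 excludes "History of or suspected severe renal impairment" (30 mL/min or less) at entry, so moderate impairment is eligible. Under section 6.1.4, subjects who fall to 30 mL/min or less "after enrollment they may remain in the study and the dosage of study drug(s) should be changed accordingly".

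Section 9.2.1 takes the rich samples on Day 4±1 at predose, 15 minutes and 1, 2, 4, 6 and 8 hours, in about 60 ceftobiprole subjects. It sets no restriction by renal function or dosing interval.

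**The concern.** At steady state with linear kinetics, dose divided by AUC equals clearance only when the AUC spans one full dosing interval. For a subject dosed every 12 hours, 8 hours is not the dosing interval, so section 9.2.3 breaks its own definition. The omitted 8-to-12-hour part makes AUC too small and CL too large, always in the same direction.

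The error falls only on subjects with reduced renal function, in whom lower clearance is expected: section 1.1.1 reports that systemic clearance correlated well with creatinine clearance. The CL listings and summaries would therefore understate the renal difference and would mix AUC over a whole interval with AUC over two-thirds of one. The rule is stated explicitly, so an analyst who follows it gets the wrong figure. It is not a detail left open for a later plan.

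**Working it through.** **Inputs from the protocol.** Infusion time T = 2 h; dosing interval 8 h (section 6.1.2) or 12 h (section 6.1.4); half-life 3 to 4 h in the Phase 1 studies (section 1.1.1); sampling times from section 9.2.1.

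**Assumptions.** One compartment, linear kinetics, steady state. The protocol gives no half-life for renal impairment, so longer values are shown as a range.

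**Step 1: the plan's own figure.** Section 6.1.1 counts 9 ceftobiprole doses in 72 h, and 72/9 = 8 h. With 8-hourly dosing, dose/AUC(0-8) divided by true CL is 1.000 at every half-life tried. Tau = 8 h is correct for the standard regimen.

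**Step 2: the same rule under 12-hourly dosing.** With k = ln 2 / half-life, AUC(0-12) at steady state equals dose/CL. The share of it lying between 8 and 12 h is

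m = [(e^(kT) − 1)/(kT)] × [(e^(−8k) − e^(−12k))/(1 − e^(−12k))]

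and estimated CL / true CL = 1/(1 − m).

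- Half-life 3 h: m = 1.271 × (0.1575 − 0.0625)/0.9375 = 0.129; ratio 1/0.871 = 1.15.
- Half-life 4 h: m = 1.195 × (0.250 − 0.125)/0.875 = 0.171; ratio 1/0.829 = 1.21.
- Half-life 8 h (assumed): m = 1.092 × (0.500 − 0.354)/0.646 = 0.247; ratio 1/0.753 = 1.33.

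The same formula gives ratios of 1.25, 1.28 and 1.38 at assumed half-lives of 5, 6 and 12 h. As half-life grows the concentration curve flattens and the ratio approaches 12/8 = 1.50, which it cannot exceed. Dose cancels, so the result is the same for 500 mg and 250 mg.

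**Step 3: effect on a renal comparison.** Suppose volume is constant and half-life doubles from 4 h (8-hourly, unbiased) to 8 h (12-hourly). True CL is then 50% lower. The reported ratio would be 0.50 × 1.33 = 0.67, an apparent drop of about a third.

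**Step 4: the correction.** With tau = 12 h, dose/AUC(0-12) divided by true CL is 1.000. No sample is planned at 12 h, but at steady state the predose concentration equals the 12-hour concentration. Applying the linear-up/log-down rule to the scheduled times, with the predose value placed at 12 h, recovers AUC(0-12) to within 0.3% at half-lives of 3 to 12 h.

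**The case against.** The strongest reply is that little depends on this. PK is listed under other objectives, the noncompartmental output is descriptive, and no test uses it. Only rich-sampled ceftobiprole subjects on 12-hourly dosing around Day 4 are affected; their number is not given, and severe impairment can arise only by decline after entry. If 5 to 15% of the 60 were affected (an assumption), the overall mean CL would move by roughly 0.05 × 15% = 0.75% to 0.15 × 33% = 5%, and by less because these subjects have lower CL. All of this stands and limits the weight of the point. It does not make the stated rule right for the subjects it covers.

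Four stronger readings are tempting, and the documents do not support them:

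- **The renal question is lost.** The aim to "explore the effects of age, sex, weight, and renal function on plasma ceftobiprole concentrations" is tied in section 3.2 to rich and sparse sampling combined, and section 9.2.3 assigns covariate evaluation to a separately reported pooled population analysis. A model using actual doses and times need not use dose/AUC(0-8).
- **The renal effect is masked.** Step 3 shows it reduced but still visible.
- **Time above MIC is wrong as well.** Section 9.2.3 does not say that it is read over, or divided by, 8 hours, and section 3.2 describes T>MIC as a percentage of the dosing interval.
- **Urinary recovery is wrong as well.** Ae is defined over the collection interval, which section 9.2.1 fixes at 0 to 8 hours.

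**Conclusion.** The point holds for the noncompartmental AUCtau and CL of rich-sampled ceftobiprole subjects dosed every 12 hours. For them, the rule in section 9.2.3 contradicts the dosing in section 6.1.4 and overstates CL by about 15 to 21% at the only half-life the protocol gives. The excess is about 33% at an assumed 8 h and always below 50%. The direction is certain under linear kinetics at steady state; the size depends on the half-life in renal impairment, which the protocol does not state, and on the one-compartment form. The consequence is smaller renal differences in the descriptive summaries. The pooled population PK analysis need not be affected, and the efficacy analysis is not affected.

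**What to change.** In section 9.2.3, replace the fixed 8 hours by the subject's actual dosing interval at the time of rich sampling (8 or 12 h), so that it agrees with section 6.1.4. For 12-hourly subjects, state how AUC(0-12) is obtained from the planned samples:

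- At steady state on an unchanged regimen, use the predose concentration as the 12-hour value.
- Otherwise, including when the regimen has just changed with renal function, extrapolate from 8 to 12 h with the terminal slope, or exclude the subject from the AUCtau and CL summaries.

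If time above MIC is reported as a percentage, use the same actual interval.

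The cost is a wording change and a small amount of PK programming, with no extra blood sample. The price is reliance on the steady-state assumption for these subjects. No change to any dose or schedule is implied.

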## 9.3. Efficacy Evaluations

### 9.3.1. Clinical Efficacy Assessments

Clinical assessments will be done during the study after review of the inclusion/exclusion criteria and documented informed consent has been obtained.

---

\* This section of the protocol has been revised. Please refer to the section of this document entitled PROTOCOL AMENDMENTS (Amendment INT-3, 22 December 2006) for a detailed description of the specific changes.

JNJ-30982081: Clinical Protocol 30982081-CAP-3001 - Amendment INT-3

At the baseline (Day 1) assessment, the following clinical signs and symptoms will be reported as present or absent:

- Cough
- Production of purulent sputum or respiratory secretions
- Presence of rales or evidence of pulmonary consolidation on chest auscultation
- Rigors or shaking chills
- Pleuritic chest pain
- Tachypnea
- Hypoxemia

At all subsequent assessments, changes in signs and symptoms will be reported in comparison with the baseline (Day 1) assessment as:

- Worsened from baseline visit
- Unchanged from baseline visit
- Improved from baseline visit
- Absent

Overall clinical assessment will be compared with the baseline (Day 1) visit:

- Worsened from baseline visit
- Unchanged from baseline visit
- Improved from baseline visit
- Cured

At the TOC assessment, the clinical outcome will be rated as follows:

**Cure:** resolution of signs and symptoms of the infection (return to pre-infection baseline), or improvement to such an extent that no further antimicrobial therapy is necessary and improvement or stabilization of chest X-ray findings.

**Failure:** death due to pneumonia occurring more than 48 hours after first infusion or a lack of efficacy (incomplete resolution of signs and symptoms of the infection, i.e., remains worse than pre-infection baseline or worsening of the chest X-ray) and requirement for additional nonstudy antibiotics to treat this episode of pneumonia after at least 48 hours of study therapy.

***Unable to evaluate:*** Discontinued early (before completing full course of study antibiotic) for any reason other than lack of efficacy and requires further antibiotics.

Subjects, who have missing data from the TOC visit, will be considered clinical failures, if they are worsened or unchanged from baseline at the EOT visit, provided that they meet no other criteria for nonevaluability.

At the LFU assessment, the TOC clinical outcome of failure or unable to evaluate will be carried forward as the LFU outcome assessment. Subjects with TOC clinical outcome of cure will be categorized at the LFU assessment as:

***Cure:*** no further antimicrobial therapy was necessary for treatment of the infection.

***Relapse:*** signs and symptoms of CAP reappeared such that additional antimicrobial therapy was necessary. Relapse will be categorized as failure at LFU.

***Unable to evaluate:*** Absence of clinical assessments at LFU, or concomitant treatment with a systemic antibiotic active against gram-positive or gram-negative respiratory bacteria, administered for a reason other than the CAP.

### **9.3.2. Microbiological Procedures and Efficacy Assessments**

Samples for appropriate culture (respiratory secretions and blood) must be obtained before the start of study therapy. Microbiological procedures will be done according to local practice. The sponsor will provide E-test® and Discs for susceptibility testing to ceftobiprole. Quantification or respiratory cultures should be recorded according to standard procedures of the local laboratory (see Attachment 3, Procedure for Collection, Culture, Susceptibility Testing, Storage, and Shipment of Microbiological Samples).

An aliquot of each potential pathogen isolated, including duplicate (follow-up) isolates from all assessments, will be shipped to the central laboratories for centralized antimicrobial susceptibility testing and pathogen identification, using Clinical and Laboratory Standards Institute (CLSI) methods. Sample handling and shipping will follow instructions provided by

the central laboratories. In cases where pathogens are characterized at the study center and centrally, the central laboratory data will be considered definitive.

The clinical investigator should be informed at the earliest occasion (overnight culture, 48-hour report) of suspected infection/colonization/superinfection with resistant pathogens.

The sponsor will provide the test kit for *L. pneumophila* urine antigen testing, which will be performed by the local laboratory.

